### Data collection, management, and analysis

#### Manovacuometry

An MVD-300 digital manovacuometer (Globalmed, Porto Alegre, Brazil) connected to a mouthpiece with a 2-mm orifice glottal closing pressure will be used. The volunteers will be placed seated, feet flat on the floor, erect spine, without supports for their upper limbs, using a mouthpiece and a nasal clip, and will be instructed to perform the MIP maneuver from the residual volume to total lung capacity (TLC), performing a maximum and sustained inspiration. There will be at least three maneuvers, a 1-minute interval between them, and reproducibility of 5–10% between maneuvers. The best among the three maneuvers will be adopted for recording the data. The predicted MIP is calculated for each individual through an equation for the Brazilian population [16].

#### Spirometry

Will be performed by using a portable spirometer (Micro Medical Microloop MK8, Micro Medical Ltd., Kent, UK). The volunteers will perform the maneuver seated, feet supported on the floor, spine erect, without support for their upper limbs and using a mouthpiece and nasal clip. At least three FVC maneuvers will be performed, and there will be a 2-minute interval between maneuvers in accordance with the reproducibility and acceptability criteria of the American Thoracic Society. Spirometric values are expressed as the percentage of the predicted normal value for the Brazilian population [17].

#### Ergospirometry

The symptom-limiting cardiopulmonary exercise test (CPET), considered the gold standard in the evaluation of functional capacity, will be performed for all patients in the study, using a ramp protocol [18] on a treadmill (Centurium 300, Micromed, Brasília, Brazil) through the ErgoPC Elite® software program associated with electrocardiogram (Micromed) with 12 channels. The respiratory variables will be evaluated by a gas analyzer (Metalyzer II, Cortex, Leipzig, Germany) obtained under standard conditions of temperature, pressure and dry (StPD), breath-by-breath, and the patient will be breathing in a non-leaking facial mask during exercise. Pressure, gas, and volume calibration of the equipment will be performed before each test. Examinations will be considered only where patients have a respiratory exchange ratio of at least 1.1 in order to ensure that patients achieve maximal effort during the examination. The test will be performed by an experienced cardiologist in an environment equipped with all emergency equipment and trained personnel. The test time is the time required to acquire a maximum stress test while maintaining patient safety since all vital signs and the electrocardiogram signal will be continually evaluated.

#### Myocardial scintigraphy with I^123^ MIBG

For myocardial scintigraphy with I^123^ MIBG, chest images will be obtained about 15 minutes after (early images) and 4 hours after (late images) receiving an intravenous injection of 185 MBq (5 mCi) of I^123^ MIBG. The images will be acquired in a tomographic gamma camera with a detector (Starcam model, General Electric Medical Systems, Milwaukee, WI, USA) with a collimator for low energy and high resolution. The energy photopeak will be centered on 159 KeV with a 20% window and 128 × 128 matrix. A static acquisition of 10 minutes will be performed in the anterior projection of the thorax in the early and late phases. A region of interest will be drawn manually over the heart (H) and over an area of nine pixels in the upper mediastinum (M) to obtain the mean counts of each of those regions, which forms the H/M ratio, it reflects the uptake of I MIBG in the nerve terminals. WR is expressed as a percentage and is calculated from the difference between early and late H/M ratios, indicating neuronal retention of the radiopharmaceutical in the area of the left ventricle. H/M values less than or equal to 1.8 and WR values greater than 19% will be considered abnormal (i.e., indicative of adrenergic hyperactivity). All patients will receive potassium iodide syrup (15 mL) orally about 1 hour before administration of I^123^ MIBG to block the thyroid gland [3]. Cardiac imaging with I^123^ MIBG is a non-invasive instrument for stratifying the risk of patients with HF by assessing sympathetic nervous system function in the heart muscle, providing treatment information and prognosis.

#### Glittre-ADL test

This test consists of carrying a backpack weighing 2.5 pounds for women and 5 kg for men, traversing a circuit with the following sequence of activities: getting up and walking out of the seated position, then walking a total distance of 10 m on the plane, interposed in its exact half (5 m) by a box with two steps to climb and two to descend, with a height of 17 cm and width of 27 cm of each step; going up and down the steps, and after traveling the rest of the course, moving three objects weighing 1 pound each placed on a shelf from the highest shelf to the lowest shelf, and then moving them to the floor; returning them to the middle shelf and higher shelf; and then returning through the entire course, sitting back in the chair and restarting another lap. The test consists of five rounds in total and individuals will be instructed to walk through them in the shortest possible time. No verbal stimulation will be given during the test. The participants will have their blood pressure, heart rate, and peripheral oxygen saturation measured and recorded before, during, and after the test through a tensiometer and stethoscope and portable pulse oximeter, respectively, in addition to perception of effort [19].

#### Ultrasonography of the diaphragm

A Sonoace R3 ultrasound (Samsung Medison, Pangyoyeok-ro, South Korea) will be used in B (thickness) and M (mobility) modes. In order to evaluate the diaphragm thickness, patients will be positioned in left lateral decubitus position and a linear low-penetration (7.5 MHz) high-resolution transducer will be positioned perpendicular to the thoracic cavity between the eighth and ninth intercostal space between the anterior and medial axillary line in such a way that it is possible to visualize two parallel bright lines that depict the pleural and peritoneal membrane. The thickness measurement will be carried out from the middle of the pleural line to the middle of the peritoneal line. An average of three final measurements of the thickness of the diaphragmatic apposition zone is performed, obtained during the functional residual capacity (FRC) (relaxed diaphragm thickness - Trel), at the end of the TLC (contracted diaphragm thickness - Tcont), and during a MIP maneuver from FRC; the latter will be used to determine the thickening rate (TR) of the diaphragm together with Trel, according to the formula:
$$ TR=\frac{Thickness\kern0.17em of\kern0.17em the\kern0.17em diaphragm\kern0.17em during\; MIP\; maneuver}{Average\kern0.17em thickness\kern0.17em of\kern0.17em the\kern0.17em diaphragm\kern0.17em in\kern0.17em the\; FRC} $$

In the diaphragm mobility evaluation, the patient will be positioned lying in the dorsal position with their thorax supported at a 45° inclination. A convex transducer (3.5 MHz) will be used in the right mid axillary line below the rib cage of the thoracic cavity, directed cranially. Patients will be instructed to breathe deeply and rapidly at the level of TLC and this maneuver will be repeated several times. The trajectory obtained between the baseline before the onset of inspiration and the plateau obtained at the end of the TLC will reveal diaphragm mobility, using the average of five measurements with a difference of less than 10% between them.

#### Quality-of-life evaluation

The Minnesota living with HF questionnaire, which is specific to the study population, will be used. It is composed of 21 items related to the causes of the problems occurring because of the heart problem. The last month should be considered to answer the questions. The scale of responses for each question varies from 0 (no) to 5 (others), where 0 represents without limitations and 5 represents maximum limitation. These issues involve a physical dimension (from 1 to 7, 12, and 13) which is highly interrelated with dyspnea and fatigue, an emotional dimension (from 17 to 21) and other issues (from numbers 8, 9, 10, 11, 14, 15, and 16), which form the total score when added to the previous dimensions [20].

#### Evaluation of the degree of satisfaction with the treatment

We have chosen to use the Patients Global Impression of Change (PGIC) scale in order to have access to interpretable information about the clinical importance of the changes in the health state perceived by the individuals when they undergo the intervention and their degree of satisfaction with it. The PGIC scale is a one-dimensional measure in which individuals rate their improvement associated with an intervention on a 7-item scale ranging from “1 = no change” to “7 = much better”. It was initially validated to determine clinically important minimal differences in degree of musculoskeletal pain [21, 22]. However, this instrument was adapted for use in our study as a way of evaluating the degree of patient satisfaction after the 3-month CR program.

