### Evaluated outcomes

The participating individuals will be evaluated on the first day of evaluation by collecting their clinical history, applying the quality-of-life questionnaire, and reading the echocardiogram. Then they will be submitted to an anthropometric evaluation (height and weight through a digital scale with anthropometer [model W300, Welmy, São Paulo, Brazil] with a capacity of 300 kg, precision of 50 g, and an anthropometer with limit of 2 m and body mass index by dividing body weight by height squared), evaluation of vital signs through a multiparameter monitor (2023, Dixtal, Manaus, Brazil), evaluation of pulmonary function through spirometry, and evaluation of respiratory muscle strength through manovacuometry. Ultrasonography will be performed on the second day to measure the diaphragm muscle thickness and mobility (secondary outcome endpoint), and maximum functional capacity (primary outcome) will be evaluated by a responsible medical professional.

The Glittre-ADL test will be performed on the third day for submaximal measurement of functional capacity (secondary outcome). Finally, the patients will be referred to a specialized hospital on the fourth day for myocardial scintigraphy (primary outcome). After all the evaluation procedures have been carried out and recorded on the corresponding file, the participants who are already randomly allocated will start their respective IMT protocols associated with CR; then the subjects will be submitted to the same evaluation process at the end of 36 sessions, along with a question that measures the degree of satisfaction with the treatment. Figure 2 and the checklist provide an overview of standardized items for clinical trials according to Standard protocol items: Recommendations for interventional trials (SPIRIT) [15].

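### The end-of-study PGIC question is labelled satisfaction with treatment, but the only rating and anchors described measure perceived improvement

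*Protocol article*

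**What the plan says.** Two sections of the protocol article deal with this question.

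*Evaluated outcomes* describes the reassessment after 36 sessions. Patients repeat the baseline evaluations, "along with a question that measures the degree of satisfaction with the treatment". The instrument is not named there.

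The section headed "Evaluation of the degree of satisfaction with the treatment" names the PGIC as that instrument. Its first sentence gives the scale two purposes: information on "the clinical importance of the changes in the health state perceived by the individuals" "and their degree of satisfaction with it". The next sentence calls the scale one-dimensional and describes the rating: "individuals rate their improvement associated with an intervention on a 7-item scale ranging from" no change (1) to much better (7). The section then says that the scale was first validated for minimal clinically important differences in musculoskeletal pain. It closes by stating that "this instrument was adapted for use in our study as a way of evaluating the degree of patient satisfaction after the 3-month CR program".

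The PGIC appears neither in the *Objectives*, which name the primary and secondary outcomes, nor among the variables listed for pre-post comparison in *Statistical methods*.

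**The concern.** The outcome carries the name of one construct and the response scale of another. Perceived improvement asks whether the patient feels better. Satisfaction asks whether the patient is content with what was provided. The two may well be correlated, but they are different quantities, and a patient can be high on one and low on the other.

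What is at stake is the sentence that can be written at the end of the trial. If the text is followed, a summary of PGIC scores will be presented as the degree of satisfaction with the treatment, although the item described never asked about it. A content but unchanged patient would score 1 and be counted as least satisfied. A patient who feels much better but was unhappy with the treatment would score 7 and be counted as most satisfied.

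**Working it through.** No arithmetic applies, because no figure in the plan depends on this point. The check sets each statement about the question beside the construct it refers to.

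| Place in the protocol article | What it states | Construct |
|---|---|---|
| *Evaluated outcomes* | what the end-of-study question measures | satisfaction |
| PGIC section, heading | what is being evaluated | satisfaction |
| PGIC section, first sentence | purpose of the scale | perceived change and satisfaction |
| PGIC section, second sentence | what the patient rates | improvement |
| PGIC section, lower anchor (1) | no change | change |
| PGIC section, upper anchor (7) | much better | change |
| PGIC section, validation history | differences in musculoskeletal pain | clinically important difference |
| PGIC section, last sentence | use in this trial | satisfaction |

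Three steps follow.

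1. Names and measurements separate. Every row that says what the result will be called or used for includes satisfaction. Every row that says what the patient rates refers to improvement or change. No satisfaction question and no satisfaction anchor appears anywhere in the article.

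2. The dual purpose cannot be met by this scale as described. A one-dimensional measure gives one score per patient. With change anchors, that score orders patients by perceived change. No second score is available from which satisfaction could be read.

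3. The statement that the scale was adapted does not resolve the mismatch. Either the adapted item still uses the anchors given, and the satisfaction label is wrong, or it uses satisfaction anchors, and the anchors given are not those of the trial. In both cases the text needs correcting.

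On reach: the PGIC is not one of the outcomes that the *Objectives* name. *Study design* says the sample size will be calculated for all study variables, so one might ask whether the PGIC enters there. Even if it did, correcting the label or the printed anchors changes no recorded score, so the calculation would be the same. Alpha and the analyses of the named outcomes do not involve this item.

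**The case against.** The best defence is that this is a declared choice of instrument and not a slip. The first sentence of the PGIC section gives both purposes openly, the origin of the scale in musculoskeletal pain is disclosed, and the authors say they adapted it. The anchors stand in a sentence about the PGIC in general, and the adapted wording may be in the full protocol or case report form, which a journal article need not reproduce.

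Much of this stands. It would be wrong to describe the problem simply as one section contradicting another, since the PGIC section holds both meanings itself. It would also be wrong to assert as fact that every patient is scored on improvement anchors, because the adapted item may differ. What does not stand is the conclusion that nothing needs changing. The article does more than leave the item out: it prints a rating and two anchors, and these do not match the outcome's name.

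A reader might infer three further things that the document does not support.

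- *That the rating is aimed at cardiac rehabilitation, which both arms receive, and so misses the randomised inspiratory training.* The phrase "as a way of evaluating the degree of patient satisfaction after the 3-month CR program" can be read as saying when the question is asked, in line with the assessment after 36 sessions. *Evaluated outcomes* gives the object as the treatment. Both arms receive rehabilitation, so a between-group comparison of any global rating would still isolate the added active training.

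- *That a between-group difference would be taken as patients preferring inspiratory training.* Nothing in the article says so. Control patients also train on the device for 30 minutes a day with a sham load, and patients are masked to group, so dislike of the daily device routine would not by itself separate the arms.

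- *That the error amounts to as much as 6 points.* That is only the width of the scale, 7 − 1 = 6. It is not an estimate of bias, and there is no satisfaction scale in the trial against which to measure a displacement.

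**Conclusion.** The concern holds as a mismatch between label and measurement. The end-of-study question is named satisfaction with the treatment, while the only rating and anchors described measure perceived improvement on a single dimension. As written, a perceived-change score would be reported as satisfaction.

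It is minor. It touches one post-treatment question outside the named primary and secondary outcomes, and leaves the sample size, alpha and main analyses as they are. No numerical size can be given, because the document has no data on how perceived change and satisfaction relate in these patients.

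The conclusion rests on one assumption: that the rating and anchors in the article are those put to patients. If they are not, the label may be right, and the error lies in the printed anchors. The text still has to be reconciled.

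**What to change.** In *Evaluated outcomes* and in the PGIC section, including its heading and last sentence, define the question as the patient's perceived change in health state and report it under that name. Drop the satisfaction label and any conclusion about satisfaction.

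If the adapted item does use satisfaction wording, keep the label and replace the stated rating and anchors with those actually used.

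Either route is a change of wording. It needs no new data, visit or analysis, and it can be made now, since *Trial status* describes the trial as still recruiting and evaluating participants. The downside of the first route is that the trial gives up a claim about satisfaction, which the item as described could not support.

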### Statistical methods

Descriptive statistics will be used, and the continuous variables will be presented as means or medians, standard deviations, and 95% confidence intervals. Categorical variables will be expressed percentages and absolute numbers. The normality of the data will be evaluated through the Shapiro–Wilk or Kolmogorov–Smirnov tests. The Levene test will be used to test the variance homogeneity.

The paired *t* test will be used for normal data or the Wilcoxon test for non-normal data to compare the pre and post intervention of adrenergic tone, maximum and submaximal functional capacity, and diaphragm mobility and thickness. The unpaired *t* test or Mann–Whitney test will be used in the comparison between the groups depending on the normality of the data, and the significance level will be accepted at a *P* value of less than 0.05. The effect size will be calculated by using Cohen’s d, and the results will be interpreted on the basis of Cohen as follows: small (0.21–0.49), medium (0.50–0.79), or large (≥0.80) [23]. All participants included in the initial assessment will be considered under the intention-to-treat according to the method of last observation carried forward. The statistical analysis will be carried out with the Statistical Package for the Social Sciences, version 22.0 (SPSS Inc., Chicago, IL, USA).

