**Methods:**

We will conduct a clinical, controlled, randomized, double-blind trial that will include sedentary men and women who are 21–60 years old and who have diagnosed systolic HF and a left ventricular ejection fraction of less than 45%. Participants will be randomly assigned to one of two groups: experimental and control. The control group will follow the conventional CR protocol, and the experimental group will follow the conventional CR protocol associated with IMT 7 days a week. The two proposed exercise protocols will have a frequency of three times a week for a period of 12 weeks. The sympathetic innervation of the cardiac muscle, the maximum and submaximal functional capacity, diaphragm mobility and thickness, and the quality of life of the participants will be evaluated before and after the intervention protocol.

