### Study design

This is a clinical, controlled, randomized, double-blind, and feasible trial developed in partnership with the Department of Physical Therapy of the Federal University of Pernambuco (*Universidade Federal de Pernambuco*) and *Hospital das Clínicas* of Pernambuco, and the patients come from the main reference centers of Recife-Brazil for the care of patients with HF. Figure 1 represents the follow-up flowchart of the study according to the CONSORT (Consolidated Standards of Reporting Trials) [12]. The sample will be calculated from the result of the first 20 patients through the GPower 3.1 software program [13] with α of 0.05 and a power of 80%. It will be calculated for all study variables, and the largest number will be increased by 20% to compensate for possible follow-up losses.

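### The between-arm question is served by within-arm tests and an unadjusted, pretest-selected group comparison; a pre-fixed baseline-adjusted ANCOVA would be more precise

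*Protocol article*

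**What the plan says.** The Statistical methods section sets out two layers of testing. A paired t or Wilcoxon test is used "to compare the pre and post intervention of adrenergic tone, maximum and submaximal functional capacity, and diaphragm mobility and thickness". An unpaired t or Mann–Whitney "test will be used in the comparison between the groups depending on the normality of the data". The choice within each pair rests on a pretest: "The normality of the data will be evaluated through the Shapiro–Wilk or Kolmogorov–Smirnov tests". No covariate or adjusted model is named, and the quantity compared between groups (post value or change) is not stated.

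The design is a two-arm randomised comparison (Abstract, Methods): "Participants will be randomly assigned to one of two groups: experimental and control". The hypothesis at the end of the Background is between-arm, rehabilitation with inspiratory muscle training (IMT) against rehabilitation without it. The Intervention section gives the same rehabilitation programme to both groups.

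The Abstract says of sympathetic innervation, functional capacity, diaphragm measures and quality of life that they "will be evaluated before and after the intervention protocol". Evaluated outcomes confirms one repeat of the same assessment after 36 sessions, with the satisfaction question added only then.

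On sizing, Study design says: "The sample will be calculated from the result of the first 20 patients through the GPower 3.1 software program", at alpha 0.05 and 80% power, for all study variables, and "the largest number will be increased by 20% to compensate for possible follow-up losses".

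**The concern.** Three features fit the trial's question poorly.

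- **Within-arm tests.** Both arms train, so both may improve. A significant pre–post change in the experimental arm mixes the effects of rehabilitation, time and IMT, and its p value cannot separate them. Yet this is the layer of testing that the section ties by name to the outcomes.
- **Between-arm test.** Every outcome named for testing has a baseline, and no model uses it as a covariate. Because the section does not choose between post values and changes, it also leaves open how far baseline enters at all.
- **Normality pretest.** A t test compares means; a Mann–Whitney test does not. With the quantity also open, four between-arm tests are possible for each outcome (2 quantities × 2 tests), and the data choose at least part of the answer.

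At stake are precision (or, at fixed power, the number of patients needed), sensitivity of a post-value comparison to chance baseline imbalance, and clarity about which result answers the IMT question.

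**Working it through.** **Inputs.** From Study design: alpha 0.05 and 80% power. The article gives no sample size, target effect, SD, allocation ratio or pre–post correlation, so there is no stated figure to reproduce. Assumed here: two-sided alpha, 1:1 allocation, equal SDs before and after, and correlation r from 0.3 to 0.8. Effects of d = 0.5 and 0.8 are illustrations, taken from the lower limits of the medium and large bands in Statistical methods.

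**Variance of the between-arm estimate**, relative to a post-value comparison: post value 1; change score 2(1 − r); ANCOVA 1 − r². Hence ANCOVA relative to change score is (1 − r²) / [2(1 − r)] = (1 + r)/2.

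- r = 0.3: 1 − 0.09 = 0.91 of post-value; 1.3/2 = 0.65 of change-score.
- r = 0.5: 0.75 and 0.75.
- r = 0.7: 0.51 and 0.85.
- r = 0.8: 0.36 and 0.90.

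Both ratios are below 1 for any r between 0 and 1, so the ordering does not depend on which quantity the plan means.

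**Patients per arm for 80% power**, before the allowance for losses: n = 2(1.960 + 0.842)² k / d², with k the variance factor above. For d = 0.5 and k = 1, 2 × 7.849 / 0.25 = 62.8, so 63.

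| r | d = 0.5: post / change / ANCOVA | d = 0.8: post / change / ANCOVA |
|---|---|---|
| 0.3 | 63 / 88 / 58 | 25 / 35 / 23 |
| 0.5 | 63 / 63 / 48 | 25 / 25 / 19 |
| 0.6 | 63 / 51 / 41 | 25 / 20 / 16 |
| 0.7 | 63 / 38 / 33 | 25 / 15 / 13 |
| 0.8 | 63 / 26 / 23 | 25 / 10 / 9 |

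At d = 0.5 the unstated choice between post value and change alone moves the requirement from 63 to anywhere between 88 and 26. Seen the other way, with 63 per arm and d = 0.5, ANCOVA takes the power of a post-value test from 80% to 84% (r = 0.3), 90% (r = 0.5) or 98% (r = 0.7).

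**Simulation check** (r = 0.6, shared gain of 0.5 SD in both arms, 6,000 trials per setting):

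- With a true IMT effect of 0.8 SD and 20 per arm, power was 69% (post), 79% (change) and 86% (ANCOVA). All three estimates averaged about 0.80, with empirical standard errors of 0.32, 0.28 and 0.26. With 10 per arm the ordering held: 40.5%, 47.2% and 53.6%.
- With no IMT effect, all three between-arm tests rejected in about 5% of trials. The paired tests were significant in exactly one arm in about 47%, 44% and 26% of trials (10, 20 and 30 per arm). The pattern of experimental arm significant and control arm not occurred in about 22%, 22% and 13%.

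**Pretest check** (4,000 trials per setting; 10, 20 and 30 per arm; test chosen by Shapiro–Wilk in each arm). The rule moved to Mann–Whitney in about 10% of truly normal data sets, and in 53%, 88% and 97% of moderately skewed (log-normal) ones. Type I error of the two-stage rule stayed between 4.6% and 5.5%.

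**The case against.** The strongest reply is that the plan already contains a valid randomised comparison and that ANCOVA only refines it. Much of that stands, and it rules out several stronger readings that a reader might infer.

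- **That the unadjusted test is biased.** It is not. Under randomisation it is unbiased on average, as the simulation shows. The gain from ANCOVA is precision and less sensitivity to chance imbalance.
- **That baseline is ignored.** The article does not say so. If changes are compared, baseline is used, and the gain is the smaller one at correlations above 0.5.
- **That the trial is small and underpowered.** No sample size is stated. The trial is to be sized for 80% power, so if the sizing matches the planned test, a less efficient test costs patients rather than power.
- **That efficacy will be claimed when one arm is significant and the other is not.** No section makes this a decision rule. The 22%, 22% and 13% measure how misleading that inference would be, not the error rate of the plan.
- **That the pretest inflates type I error.** The simulation found no material inflation. What remains is a test and target that are not fixed in advance and can differ between outcomes.
- **That every outcome has a baseline.** The satisfaction scale does not.

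The size of the gain also depends on a correlation that the article does not give and that need not be the same for scintigraphy, exercise testing, the Glittre test and ultrasound. At r = 0.3 the gain over a post-value test is small.

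The reply does not remove the core. The section fixes a set of tests, leaves the compared quantity open, and omits a covariate that will be collected in any case.

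**Conclusion.** The point holds as one of precision and specification, not of validity. The plan should be changed, but it is not unsound as it stands.

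Within-arm p values do not answer the IMT question. The between-arm test is valid but less precise than ANCOVA at any correlation between 0 and 1: ANCOVA has 91% to 36% of the post-value variance and 65% to 90% of the change-score variance for r from 0.3 to 0.8. Those percentages rest on the assumed range of r, equal SDs before and after, and a linear relation with baseline; the direction of the gain does not depend on the particular r. The pretest matters because it leaves the test and its target to the data.

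**What to change.** Amend Statistical methods, with a date and before any unblinded analysis, as follows.

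1. For each outcome with a baseline, make the between-arm comparison an ANCOVA of the post value on arm and baseline, and report the adjusted difference with its 95% confidence interval.
2. Name one method of inference in advance, for example ANCOVA with a robust-variance p value, and drop the choice by normality pretest.
3. Report within-arm changes descriptively, without p values.
4. Analyse the satisfaction scale as an unadjusted between-arm comparison, since it has no baseline.
5. In Study design, base the sample size on the same ANCOVA, using the pre–post correlation seen in the first 20 patients with an allowance for how uncertain that estimate is.

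No new data or visits are needed. The cost is the amendment itself. Trial status says that recruitment began in May 2015, and the first 20 patients' results feed the sizing. The amendment should therefore state its reason and whether any outcome data had been seen by group when it was made. Check that the SPSS version named in the article supplies the chosen robust variance before fixing it.

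### Results are to be read through Cohen's labels on a point estimate of d, with no interval and no exception for rank-tested outcomes, and no between-arm difference with a 95% CI is named as the estimate

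*Protocol article*

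**What the plan says.** All the analysis statements are in the Statistical methods section of the protocol article.

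- Effect measure: "The effect size will be calculated by using Cohen’s d". The article does not say whether d is for the change within an arm or the contrast between arms.
- Reading rule: "the results will be interpreted on the basis of Cohen as follows: small" for d from 0.21 to 0.49, medium from 0.50 to 0.79, and large from 0.80 upwards. No interval for d is mentioned.
- Descriptive summaries: "the continuous variables will be presented as means or medians, standard deviations, and 95% confidence intervals".
- Between-arm test: the unpaired t "test or Mann–Whitney test will be used in the comparison between the groups depending on the normality of the data", judged at P < 0.05. Before-and-after comparisons switch in the same way between the paired t and Wilcoxon tests.

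On size, the Study design section says "The sample will be calculated from the result of the first 20 patients through the GPower 3.1 software program", "with α of 0.05 and a power of 80"%. The calculation is to be done for every variable, and the largest answer is raised by 20%. No final number is given.

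**The concern.** There are two weaknesses in what the section states.

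First, the rule turns a point estimate into a verdict. A d of 0.50 is called medium whether it comes from 10 or 100 patients per arm, although its uncertainty differs greatly. A standardised label also cannot show whether a change in washout rate, H/M ratio or peak oxygen uptake matters to a patient. The Discussion wants the trial to help elucidate clinical benefit. The estimate that answers this is the difference between IMT and sham in the outcome's own units with its interval, and the section does not name it.

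Second, the rule does not follow the test. Once an outcome is judged non-normal, the comparison is made on ranks. The stated effect is still a difference in means divided by a standard deviation, and the stated spread is still the standard deviation, even beside a median. The P value and the effect size then describe different quantities.

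At stake is how the results are read: an abstract could report a medium effect on a primary outcome when the data are also compatible with none.

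**Working it through.** The article gives no N, target effect or standard deviation, so there is no figure of its own to reproduce. The check takes a range of sizes. Assumptions: two arms of n patients (1:1), normal data, two-sided 5% level, d as the between-arm contrast. The cut-offs 0.21, 0.50 and 0.80 are from the article.

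**1. Chance of a label with no true effect.** With equal arms, t = d·√(n/2) on 2n − 2 degrees of freedom, so P(|d| ≥ c) = 2·P(T ≥ c·√(n/2)). For n = 10 and c = 0.50, t = 0.50 × √5 = 1.118 on 18 df, giving 27.8%.

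**2. Size of d needed for P < 0.05.** d_crit = t(0.975, 2n − 2)·√(2/n). For n = 10: 2.101 × 0.447 = 0.94.

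**3. Chance of medium or more without significance.** Where d_crit exceeds 0.50, this is P(|d| ≥ 0.50) − 5%; otherwise it is zero.

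**4. 95% CI for an observed d of 0.50**, by inverting the noncentral t.

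| n per arm | t at d = 0.50 (df) | P(\|d\| ≥ 0.50) | P(\|d\| ≥ 0.21) | d_crit | medium or more, not significant | 95% CI for d = 0.50 |
|---|---|---|---|---|---|---|
| 10 | 1.118 (18) | 27.8% | 64% | 0.94 | 22.8% | −0.40 to 1.38 |
| 20 | 1.581 (38) | 12.2% | 51% | 0.64 | 7.2% | −0.13 to 1.13 |
| 30 | 1.936 (58) | 5.8% | 42% | 0.52 | 0.8% | −0.02 to 1.01 |
| 40 | 2.236 (78) | 2.8% | 35% | 0.45 | 0 | 0.05 to 0.94 |
| 64 | 2.828 (126) | 0.5% | 24% | 0.35 | 0 | 0.15 to 0.85 |

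The chance rates count both directions; in favour of IMT alone they are half. Ten per arm is the size of the first 20 patients. Sixty-four per arm is the t-test size for 80% power at d = 0.50.

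**5. Rank-tested outcomes.** Take lognormal data with log-scale SD σ (an assumption) and shift one arm by 0.5σ on the log scale. A rank test gives the same result on the log and raw scales. On the raw scale, d = (e^(0.5σ) − 1) / √[(e^(σ²) − 1)(e^σ + 1)/2].
- σ = 1: 0.649 / 1.787 = 0.36.
- σ = 0.5: 0.284 / 0.613 = 0.46.

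On the log scale d is 0.50, which is medium; on the raw scale both values are small. The label moves while the rank comparison does not.

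**6. Does this produce open conflict between test and label?** Simulation with 15 per arm, lognormal, log-SD 1, median ratio 1.8 (all assumed): |d| ≥ 0.50 with a non-significant Mann–Whitney test in about 24% of datasets. Normal data with the same standardised shift (ln 1.8 = 0.588) and a t test: about 26%. The sign of d opposes that of the Hodges–Lehmann shift in about 8% of the lognormal datasets, but in under 0.1% does this coincide with |d| ≥ 0.50.

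**The case against.** The strongest reply is that the label does not stand alone. A between-group test at P < 0.05 is planned, and nothing says the label replaces it. A reader might infer that patients and clinicians would be told of a medium effect with no sign that the data fit no effect. The text does not support that, because the P value would be such a sign. What survives is narrower: the article does not say which governs when they differ, and in small arms they can differ.

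A reader might also infer that chance alone would often earn a medium label in this trial. That needs small arms. The first 20 patients are the input to the size calculation, not the final size. At 40 per arm the rate is below 3%, and every medium label is then also significant. This part of the reply stands.

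A third tempting reading is that the benefit is never estimated in clinical units. That goes too far. Means or medians with SDs and 95% CIs are planned in original units, and a difference of means can be worked out from arm means, SDs and numbers.

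Nor do the simulated non-normal data show that ranks and means collide often. The normal data behave almost the same way (about 26% against 24%), so that figure mainly reflects low power. The mismatch is one of coherence: two different quantities are reported as one result.

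Finally, an article may leave the form of the contrast to a fuller plan. That excuses missing detail. It does not excuse a stated interpretation rule that is itself poor.

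**Conclusion.** The point holds in a limited form. The article fixes a reading rule that labels the point estimate of d without an interval. The rule does not change when the test moves to ranks, and no between-arm difference with a 95% CI is named as the estimate to interpret.

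The practical size depends on an N that is not stated. Under no true effect, a label of medium or more that is not significant would arise in about 23% of comparisons at 10 per arm, 7% at 20, under 1% at 30 and none at 40 or above. These figures assume equal arms, normal data, a two-sided 5% level and d taken between arms. The loss of clinical units in the interpretation and the mismatch with rank tests do not depend on N. No test, sample size or data item is affected, so this is a worthwhile and cheap improvement in reporting rather than a threat to the trial's validity.

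**What to change.** In Statistical methods, replace the sentence on effect-size labels with wording to this effect:

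- For each outcome, report the between-arm difference (IMT minus sham) in its own units with a 95% CI, and base conclusions on that estimate and interval.
- For outcomes tested by ranks, give medians with quartiles and the Hodges–Lehmann shift with its 95% CI, in place of medians with SDs and Cohen's d.
- Keep d, if wanted, only as a supplementary figure for the between-arm contrast, with its own CI.

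The cost is a change of analysis wording, with no new data or visits. The drawback is presentational: wide intervals will look less favourable than the labels, particularly if the arms stay small.
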